Chronic lung disease (CLD)	Diagnosis of CLD, as recorded on eCRF	Diagnosis of CLD between date of randomisation and date of hospital discharge	Proportion of infants who are mechanically ventilated or on nasal CPAP or in supplemental oxygen at 36 weeks corrected gestational age, per group	Hospital discharge
Brain injury	Diagnosis of intraventricular haemorrhage (grade 3 or 4), periventricular leukomalacia or hydrocephalus (requiring a shunt) on cranial ultrasound, recorded on eCRF	Diagnosis of brain injury (as per definitions) between date of randomisation and date of hospital discharge	Proportion of infants with recorded evidence of brain injury (grade 3 or 4 intraventricular haemorrhage, periventricular leukomalacia or hydrocephalous requiring shunt, per group	Hospital discharge
Blood glucose/hypoglycaemia	Number of blood glucose tests, as recorded on eCRF. Number of blood glucose tests indicating hypoglycaemia (< 2.2 mmol/L). Number of blood tests indicating severe hypoglycaemia (< 1.0 mmol/L)	Number of blood glucose tests, between date of randomisation and date of hospital discharge. Number of blood glucose tests < 2.2 mmol/L, between date of randomisation and date of hospital discharge. Number of blood glucose tests < 1.0 mmol/L between date of randomisation and date of hospital discharge	Mean (and SD) and/or median (and IQR), per group. Mean (and SD) and/or median (and IQR), per group. Mean (and SD) and/or median (and IQR), per group	Hospital discharge. Hospital discharge. Hospital discharge
Hospital visits	Number of hospital visits, including day care and overnight admissions, as recorded on 6-week parent-completed questionnaire	Number of hospital visits between date of hospital discharge and 6 weeks corrected gestational age	Mean (and SD) and/or median (and IQR), per group	6 weeks corrected gestational age
Parental satisfaction and wellbeing	Preterm birth experience and satisfaction scale (P-BESS) [21], completed by parents	P-BESS total score (and subscales for interpersonal care, information and explanations, lack of confidence in staff) at 6 weeks corrected gestational age	Mean (and SD) and/or median (and IQR), per group	6 weeks corrected gestational age

^1^Indeterminate cases will be subject to a blinded endpoint review to make a final determination

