### Adverse events

As adverse events are commonly encountered in preterm infants receiving neonatal care, they will be recorded in the infant’s medical notes as per usual practice, from the commencement of the randomised feeding strategy until hospital discharge. Adverse reactions are thus collected as outcomes and will not need to be reported separately via an adverse event reporting process. Blood glucose levels will be monitored routinely for all infants, recorded in the trial eCRF and provided in meeting reports to the independent data monitoring committee (DMC). Coding of adverse events (e.g. MedDRA) will not be undertaken. Serious adverse events (SAEs), including death, will be reported as such by the principal investigator, or delegate, reporting within 24 h of being made aware of the event, using an SAE form, sent via email to a dedicated SAE reporting mailbox at NCTU. Reporting will be aligned with the standard operating procedure (SOP) at the Nottingham Clinical Trials Unit. The chief investigator, or delegate (neonatologist), has responsibility for the review of all SAEs, to assess causality. Late-onset sepsis (microbiologically confirmed or clinically suspected), necrotising enterocolitis (Bell’s stage 2 or 3) or other known complications of prematurity will not be reported as serious adverse events. Only SAEs that are deemed to be related to the trial interventions will be followed up until resolution. If an SAE is unexpected, it will be classified as a SUSAR (serious unexpected suspected adverse reaction). All SUSARs will be reported by NCTU to the ethics committee within 15 days of being notified, and all principal investigators will be notified. The DMC will review all reported SAEs and neonatal outcome data at regular intervals throughout the trial, in line with the DMC charter.

Insurance and indemnity for infants and NHS trial staff is covered within the NHS Indemnity arrangements for clinical negligence claims in the NHS. No special compensation arrangements apply to this trial, though parents may have recourse to the NHS complaints procedure.

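### Hypoglycaemia is measured only as counts of low glucose tests per infant, so the comparison depends on testing frequency and does not show how many infants were affected

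*Protocol article*

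**What the plan says.** In the protocol article, Table 1 (Outcomes), the blood glucose/hypoglycaemia row has three components, each a count per infant:

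- all tests: "Number of blood glucose tests, as recorded on eCRF";
- low tests, below 2.2 mmol/L: "Number of blood glucose tests indicating hypoglycaemia";
- severe low tests, below 1.0 mmol/L: "Number of blood tests indicating severe hypoglycaemia".

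The metric column fixes the window. For the second component it reads "Number of blood glucose tests < 2.2 mmol/L, between date of randomisation and date of hospital discharge", and the other two use the same window. The aggregation for all three is "Mean (and SD) and/or median (and IQR), per group". No component is the number or proportion of infants with a low value. In the same table, late-onset sepsis, NEC, ROP, chronic lung disease and brain injury are all aggregated as proportions of infants.

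Four other places bear on this:

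- Randomisation and blinding says that investigators and families cannot be blinded.
- The text under Table 2 (Trial assessments and procedures) says that no specimens are taken specifically for the trial and that sampling follows usual care.
- Adverse events says "Blood glucose levels will be monitored routinely for all infants", with values recorded in the eCRF and supplied to the DMC. It states no common testing schedule.
- Statistical analysis says that secondary outcomes will be compared with multilevel regression models suited to the type of outcome.

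**The concern.** The intervention gives milk from the day of birth in place of IV fluids or parenteral nutrition, so blood glucose is a natural safety question, and the protocol singles it out for DMC reports. A count of low tests mixes four things: how many infants became hypoglycaemic, how often each infant was tested, how many repeat tests were taken during one low episode, and how long the infant stayed in hospital. Only the first is what a clinician or parent wants to know.

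Staff who know the allocation decide on testing within usual care, so the second and third could differ by arm. The fourth is the primary outcome, and the trial hopes to change it. A difference in counts could then appear without any difference in risk. A real difference in the number of infants affected could also be diluted, or hidden altogether if the median is the summary reported.

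This concerns the stated metric and aggregation. The Outcomes section says that Table 1 supplies those elements for every outcome, so it is not a detail held over to an analysis plan that is not shown.

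**Working it through.** **The plan's own figures.** The documents give no hypoglycaemia rate, testing frequency or power for this outcome. The only figure to reproduce is the sample size for length of stay, which is needed here for the effective sample size.

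- Per arm: 2 × (1.960 + 1.282)² × 13² / 2² = 888, so 1776 in total against the stated 1778.
- Mean infants per pregnancy: 0.836 + 2 × 0.15 + 3 × 0.014 = 1.178.
- Design effect with ICC 0.82: 1.178 / (0.836 + 0.30/1.82 + 0.042/2.64) = 1.159. This gives 1778 × 1.159 / 0.98 ≈ 2102. The simpler form, 1 + 0.178 × 0.82 = 1.146, gives 2079. The stated 2088 lies between them.
- Effective infants per arm: (2088/2) / 1.159 ≈ 901. This borrows the length-of-stay ICC for hypoglycaemia, which is an assumption.

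**Effect of testing frequency (assumed inputs).** Take 10 tests per infant in one arm, and the same risk q of a low reading per test in both arms. Expected low tests = q × tests. P(at least one) = 1 − (1 − q)^tests.

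| q | Tests | Mean low tests | Infants with any low test |
|---|---|---|---|
| 2% | 10 vs 12 | 0.20 vs 0.24 | 18.3% vs 21.5% |
| 2% | 10 vs 15 | 0.20 vs 0.30 | 18.3% vs 26.1% |
| 5% | 10 vs 12 | 0.50 vs 0.60 | 40.1% vs 46.0% |
| 5% | 10 vs 15 | 0.50 vs 0.75 | 40.1% vs 53.7% |

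The mean count rises in proportion to testing. Low tests divided by all tests stay at q in both arms.

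**Chance of a nominally significant difference in mean counts when per-test risk is equal.** Normal approximation, SE = √(φ(μ₀ + μ₁)/901), where φ = 1 is Poisson variance and φ = 3 is threefold overdispersion.

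| q | 20% more tests, φ = 1 / φ = 3 | 50% more tests, φ = 1 / φ = 3 |
|---|---|---|
| 2% | 44% / 18% | 99% / 69% |
| 5% | 82% / 38% | 100% / 97% |

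Example: q = 5%, 20% more tests, φ = 1. The SE is √(1.10/901) = 0.0349, the difference is 0.10, z = 2.86, and Φ(2.86 − 1.96) ≈ 0.82. With equal testing the figure is the nominal 5%.

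**Repeat tests.** One infant with k low readings and k infants with one each add the same amount to the mean. The stated summaries do not separate these cases unless the event is common enough to move the median or quartiles.

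**Uncommon events.** If fewer than 25% of infants have any event, the 75th percentile is 0, so the median (IQR) is 0 (0 to 0). Suppose 1% against 2% of infants have one value below 1.0 mmol/L each. The medians are both 0 and the means are 0.01 against 0.02. As an infant-level proportion with 901 effective infants per arm, power to detect a doubling is 23% from 0.5%, 42% from 1%, 70% from 2% and 98% from 5%.

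**The case against.** There is a good case that the row is adequate.

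1. *The denominator is already there.* Total tests is a component of the same outcome over the same window, so unequal testing would be visible and low tests per test could be derived. This stands. It limits the harm, but no stated metric makes that adjustment, and group means cannot recover the number of infants affected.
2. *The aggregation column is descriptive.* The Statistical analysis section permits a count model with the number of tests as an offset, and an analysis plan may specify one. This stands for the model. It does not supply an infant-level measure, because Table 1 has fixed the outcome as counts.
3. *The mean would still show rare events.* True, as the 0.01 against 0.02 example shows. The difficulty is confined to reports that give the median alone, which the and/or wording allows.
4. *A proportion does not cure the bias.* Also true. At q = 5% with 10 against 15 tests, the proportions are 0.401 and 0.537. The risk ratio is 1.34, and the odds ratio is (0.537/0.463)/(0.401/0.599) = 1.73, against a count ratio of 1.50. The proportion answers a different question; the per-test comparison is what addresses testing frequency.
5. *Other counts in Table 1, such as central lines and hospital visits, are summarised the same way.* True, so the layout is not an oddity. Those counts are the quantity of interest in themselves, whereas a count of low tests stands in for a clinical condition.

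A reader might go further and infer that the comparison is biased or uninformative, or that severe counts will be close to zero. The documents do not support this. Open-label care allows testing to differ between arms, but nothing shows that it does, and no rate of severe hypoglycaemia is given. Nor is this outcome ranked as key: it is one of a long list of unranked secondary outcomes, and the DMC receives the glucose data in any case.

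**Conclusion.** The point holds in a limited form. As defined, the hypoglycaemia comparison is at risk of ascertainment bias and hard to interpret, because it counts tests rather than infants, over a window that ends at the primary outcome. The size cannot be read from the documents. Under the assumptions above, 20% more testing in one arm raises the mean count by 20% and gives an 18% to 82% chance of a significant result with equal per-test risk. With equal testing and equal stay there is no such distortion, and what remains is that the number of infants affected is not reported. The statement about the median needs no assumed rate: it applies to any event seen in fewer than a quarter of infants. The effect of the window is directional only, since the documents do not say when during the stay tests are taken. This is worth correcting, but it does not touch the primary analysis.

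**What to change.** In the blood glucose/hypoglycaemia row of Table 1 and in the analysis plan:

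- Add the number and proportion of infants with at least one value below 2.2 mmol/L, and with at least one below 1.0 mmol/L. Compare them with the multilevel binary model used for the other binary outcomes. A risk ratio or risk difference is easier to read here than an odds ratio, for the reason shown under point 4 of the objections.
- Compare the counts of low tests relative to tests performed, for example with a multilevel count model that has the log number of tests as offset. State how infants with no recorded test are handled, since the offset is undefined for them.
- Keep total tests per arm beside both results as context.

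The cost is one or two extra analyses from data already in the eCRF, and an edit to the outcome definition before database lock. Neither measure is sufficient alone. The proportion still rises somewhat with testing. The per-test rate can shift if extra tests are triggered by a low reading or are added in infants at low risk. They should be reported and read together.

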### Sample size and recruitment

Our sample size calculation has been based upon detecting a between group difference in means of length of stay of 2 days. Input from our parent representatives suggests that from a family perspective even a short reduction in length of hospital stay could make a huge difference to parents. In addition, from a cost-saving perspective, a reduction in length of stay of 2 days for this population of infants could result in £5.6 m annual savings for the NHS in England and Wales and > 12,000 days of increased neonatal cot capacity.

Data from audits and previous studies suggest that the distribution of length of hospital stay in this population is approximately normal. To detect a difference in means of 2 days between the two groups with 90% power, 1:1 allocation and 5% two-sided significance requires 1778 infants, assuming a standard deviation of 13 [23, 24]. Allowing for 2% non-collection of the primary outcome data due to death, no consent for data collection after oral assent and infants remaining in hospital at the end of data collection and accounting for clustering will require 2088 infants and recruitment of approximately 1770 women. The inflation to account for clustering assumes that 15% and 1.4% of pregnancies will be twin and triplets respectively and that the intracluster correlation coefficient for length of hospital stay for infants from the same pregnancy is 0.82 [4].

### Participant enrolment and consent

The flow of women and infants throughout the trial is shown in Fig. 1. As the infant must be randomised within three hours of birth, a time during which the woman is recovering from giving birth and that is emotionally fraught and potentially difficult for families, a two-stage consent pathway will be used. Wherever possible, women will be approached antenatally and asked to consider participation in the trial. At around the time of antenatal counselling consultation, women will be given study information, have the opportunity to discuss the study and ask questions and give full written informed consent if they are willing to do so. For these women, once they have given birth, infant eligibility will be checked and the infant(s) will be entered into the trial, unless the mother expresses that she has changed her mind. For some women, receiving information and providing consent antenatally may not be possible due to the rapid and unexpected nature of preterm birth. During labour and postnatally, these women can be approached via an oral assent pathway. This involves a member of the neonatal team inviting the woman to participate and giving the minimal information required to make a decision. A shorter, simplified participant information sheet and/or a short animation film may be used to support this discussion. The decision to participate will be documented in the medical notes and full written informed consent will be obtained later (ideally ≤ 72 h). This two-stage consent pathway has been used successfully in a previous neonatal trial [24] and features as part of guidance from the Royal College of Obstetricians and Gynaecologists (RCOG) [25]. Sites will be fully trained in the two-stage consent pathway and will be provided with a range of supplementary materials to support oral assent conversations which include a recorded webinar, video showing examples of discussions and additional documentation. Women are asked to give their optional consent to be contacted for longer-term follow-up of their infant(s) and for later educational outcomes.

**Fig. 1 Fig1:**
[figure not shown]
Participant flow diagram

### Randomisation and blinding

The unit of randomisation is the mother to ensure that a mother-infant(s) dyad is treated as a unit. This will also enable antenatal consent and facilitate early commencement of the intervention. In addition, it will ensure that siblings from multiple pregnancies are assigned to the same group. Parents have told us this is important to them as they would not like to feed their infants differently unless there was a medical reason to do so. Randomisation will be performed on a 1:1 ratio, using a secure web-based system, developed and maintained by the Nottingham Clinical Trials Unit (NCTU), which will conceal allocation sequence. Randomisation will use a minimisation algorithm, with a random element, to ensure balance on important prognostic factors: neonatal unit, single or multiple birth, gestational age at birth, birth weight centile and whether IV fluids were started prior to randomisation. Randomisation will be undertaken by the principal investigator, clinician or other study team member within three hours from the recorded time of birth. This is to ensure infants randomised to full milk feeds can receive the intervention with minimal risk of receiving IV fluids and should help prevent contamination between groups.

It is not possible to blind investigators and families due to the nature of the intervention. Unblinding is therefore not relevant as this is an open-label trial. However, the trial statistician will remain blinded throughout the trial. To objectively assess the primary outcome, a secondary outcome measure to objectively assess discharge criteria is included and a blinded endpoint review committee (BERC) will also be established to examine cases of late-onset sepsis and necrotising enterocolitis where the diagnosis is unclear.

### Trial assessments and procedures

All trial assessments and procedures are outlined in Table 2. Most outcome data will be collected during the infant’s hospital admission. A daily feeding log will be completed until the infant receives at least 140 ml/kg/day of feeds, sustained for 3 consecutive days. For infants who are transferred to another hospital, i.e. a continuing care site, a paper transfer pack will accompany the infant with information on trial participation and data collection will continue. To collect data at 6 weeks corrected gestational age, an online questionnaire (or paper if preferred) will be sent to women; reminders will be sent to increase response-rates.

**Table 2 Tab2:**
[figure not shown]
Schedule of assessments

No laboratory specimens will be collected specifically for the trial. Any samples taken are in line with usual care and results will only be recorded in the eCRF if relevant (e.g. blood glucose, late-onset sepsis).

No specific provision has been included for the care of infants outside of the trial; clinical care will be as per usual care, in line with the pragmatic nature of the trial.

### Adverse events

As adverse events are commonly encountered in preterm infants receiving neonatal care, they will be recorded in the infant’s medical notes as per usual practice, from the commencement of the randomised feeding strategy until hospital discharge. Adverse reactions are thus collected as outcomes and will not need to be reported separately via an adverse event reporting process. Blood glucose levels will be monitored routinely for all infants, recorded in the trial eCRF and provided in meeting reports to the independent data monitoring committee (DMC). Coding of adverse events (e.g. MedDRA) will not be undertaken. Serious adverse events (SAEs), including death, will be reported as such by the principal investigator, or delegate, reporting within 24 h of being made aware of the event, using an SAE form, sent via email to a dedicated SAE reporting mailbox at NCTU. Reporting will be aligned with the standard operating procedure (SOP) at the Nottingham Clinical Trials Unit. The chief investigator, or delegate (neonatologist), has responsibility for the review of all SAEs, to assess causality. Late-onset sepsis (microbiologically confirmed or clinically suspected), necrotising enterocolitis (Bell’s stage 2 or 3) or other known complications of prematurity will not be reported as serious adverse events. Only SAEs that are deemed to be related to the trial interventions will be followed up until resolution. If an SAE is unexpected, it will be classified as a SUSAR (serious unexpected suspected adverse reaction). All SUSARs will be reported by NCTU to the ethics committee within 15 days of being notified, and all principal investigators will be notified. The DMC will review all reported SAEs and neonatal outcome data at regular intervals throughout the trial, in line with the DMC charter.

Insurance and indemnity for infants and NHS trial staff is covered within the NHS Indemnity arrangements for clinical negligence claims in the NHS. No special compensation arrangements apply to this trial, though parents may have recourse to the NHS complaints procedure.

### Data management

All trial data will be collected by site staff delegated to do so and entered onto a trial specific database (eCRF) with infants only identified by their unique trial number and initials. Using MACRO (Elsevier), the database will be developed and maintained by NCTU staff. Access to the database will be restricted and secure. Sites will be provided with paper workbooks to assist them with data collection. Missing or spurious data will be queried in a timely manner throughout the trial, in accordance with the trial data management plan. To facilitate contact with families at 6 weeks corrected gestational age, contact details will be collected and entered into an online secure system, developed and maintained by NCTU staff. This data is held separately to the deidentified trial data collected. Access to contact details is restricted to those involved in the follow-up phase, as authorised by the chief investigator.

### Statistical analysis

Analysis and reporting of the trial will be in accordance with the Consolidated Standards of Reporting Trials (CONSORT) [26] guidelines. All analyses will be outlined in a detailed Statistical Analysis Plan agreed prior to database lock. No interim analyses are planned. The primary comparative analyses will be conducted according to randomised allocation with due emphasis on confidence intervals for between-group comparisons.

The primary outcome will be analysed using linear mixed models to compare the mean length of hospital stay between groups, adjusting for minimisation variables and accounting for the correlation between outcomes for infants born from a multiple pregnancy. The estimated between group effect will be presented using the difference in means, with a 95% confidence interval. Secondary outcomes will be analysed similarly using appropriate multilevel regression models, dependent on the type of outcome variable. The between group effect will be reported using an appropriate effect estimate along with a corresponding 95% confidence interval.

The primary approach to between-group comparative analyses will be by modified intention-to-treat (i.e. including all participants who have been randomised and without imputation of missing outcome data). In particular, the primary analysis will exclude the small number of deaths that might occur before discharge, but sensitivity analysis will be performed by imputing the primary outcome with the worst observed length of stay for infants who died prior to discharge to check that this does not influence the findings. A further sensitivity analysis will assess the effect of compliance with the allocated feeding strategy through complier average causal effect (CACE) analysis.

Appropriate interaction terms will be included in the primary regression analyses to conduct subgroup analyses according to gestation at birth and birth weight centile, but this analysis will be regarded as exploratory as the study is not powered to detect interactions. Interpretation of any subgroup effects will be based on the treatment-subgroup interaction and 95% confidence interval.

A within-trial economic analysis will be conducted from an NHS and personal social services perspective. Resource data will be collected prospectively and unit costs will be obtained from routine sources. The main cost-effectiveness analysis will be based on the cost per reduction in days in care. A longer-term projection of costs and benefits will be estimated through decision analytical modelling. Appropriate sensitivity analyses will be undertaken to account for any uncertainty.

